## Abstract

**Background:**

Mild cognitive impairment (MCI) is a transition state between asymptomatic stage and dementia. Amnestic MCI (aMCI) patients who mainly present with memory deficits are highly likely to progress to Alzheimer’s disease (AD). At present, no broadly effective drug therapy is available to prevent the progression from memory deficit to dementia. Cognitive control training, which has transfer effects on multiple cognitive capacities including memory function in healthy old adults, has not yet been applied to aMCI.

**Methods/Design:**

In this single-center, randomized double-blind placebo-controlled study, 70 aMCI patients will be recruited and randomly assigned to the training and control groups. The intervention is an Internet-based cognitive control training program performed for 30 min daily, five days per week, for 12 consecutive weeks. Neuropsychological assessment and structural and functional magnetic resonance imaging (MRI) will be performed at baseline and outcome. Primary outcomes are changes of episodic memory retrieval function. Secondary outcome measures are neuroplasticity changes measured by functional and structural MRI.

**Discussion:**

In this study, an Internet-based cognitive control training program is adopted to investigate whether cognitive control training can enhance the retrieval of episodic memory in aMCI patients. The combination of multi-modal MRI and neuropsychological tests could have a good sensitivity in evaluating the effects of cognitive control training and could also uncover the underlying neural underpinning.

**Trial registration:**

ClinicalTrials.gov, NCT03133052. Registered on 21 April 2017.

**Electronic supplementary material:**

The online version of this article (10.1186/s13063-018-3143-0) contains supplementary material, which is available to authorized users.

## Background

Alzheimer’s disease (AD) is the most common age-related neurodegenerative disorder. Cardinal AD symptoms are memory impairment and cognitive function decline. Mild cognitive impairment (MCI) refers to the transition state between the asymptomatic stage and dementia [1]. According to the affected cognitive domain, MCI is generally divided into amnestic MCI (aMCI) and non-amnestic MCI. aMCI is primarily manifested by memory deficits with or without other cognitive impairments, while non-amnestic MCI is mainly characterized by cognitive impairments other than memory deficits, such as decline in executive function, linguistic function, visuospatial function, and attention [2].

Approximately 10–15% of aMCI patients annually progress to AD and up to 80% progress to AD dementia within six years [3], although a proportion of this group never progress to develop dementia [4, 5]. Up to now there are no effective drug therapies available to prevent or slow this process. An efficacious non-medical approach is thus urgently required for MCI intervention.

Cognitive training is a promising non-drug alternative to slow MCI-to-AD progression. Studies show that game-style cognitive training can effectively improve the cognitive function of elderly individuals [6, 7] and even reverse the age-dependent decline in cognitive capacity. In general, recent meta-analyses further revealed promising training effect in MCI [8, 9] with comparable training improvement between MCI and healthy adults [8].

It remains unclear whether cognitive training is effective in promoting memory function, especially episodic memory function in aMCI. Episodic memory [10], a subtype of long-term memory, has the ability to remember past events as well as details about the context (e.g. times, places, persons). For instance, it enables us to form a detailed autobiographical event and represent our past experiences [11, 12]. Episodic memory consists of three distinct processes: encoding; storage; and retrieval. Encoding transforms the information of external stimuli or activates cognitive processes and aggregates the information. Followed by the encoding phase, information storage is triggered, which allows events to be maintained and recomposed into the long-term memory. Finally, retrieval processes are required to reactivate its mental representations and return the individual to his or her conscious experience of the event [13]. Episodic memory impairment is the earliest and most clinically significant neuropsychological manifestation of aMCI as well as an early predictor of progression to AD [3].

A common approach to enhance the memory function of the aMCI patients was mnemonic strategy training. Such training protocols, however, have yielded controversial results, as both positive [14, 15] and negative findings [16] were reported. Moreover, a meta-analysis found that memory intervention alone had limited efficacy for improving objective memory and other cognitive functions compared to the positive control group [17].

Another approach to enhance memory function is cognitive control training. Cognitive control refers to how an individual stores, plans, and controls relevant information according to task demands in the course of information processing. It involves coordinating the retrieval by working memory, inhibiting automatic retrieval, updating the retrieved strategy, attention control, and selection [18]. Cognitive control training aims to enhance an individual’s cognitive control abilities (e.g. sustained attention, working memory, and task switching) [19]. Several investigations [20–23] have found that cognitive control training can exhibit transfer effects on multiple cognitive capacities, even those not directly targeted by the specific training task, including short-term memory and delayed recall in healthy old adults [24–26]. Moreover, Carreti et al. [27] demonstrated that cognitive control training enhanced the long-term memory performance of MCI patients. Recent meta-analyses further suggest that cognitive control training such as working memory training is the most effective training in enhancing cognitive function across healthy and functional impaired older adults [8]. However, as most studies have combined different types of MCI, it remains unclear whether cognitive training can enhance the episodic memory in aMCI.

This trial is the first study to test the efficacy of cognitive control training on episodic memory retrieval function in aMCI patients using a double-blinded, randomized controlled trial design. A further character of the current trial is investigating the neural underpinning of the cognitive control training. While previous studies have shown neural plasticity including functional response and connectivity, and both gray and white matter anatomical change [19, 28–32], how the critical cognitive control related network compensate the memory function is unclear. Recent studies in healthy older adults have showed that older adults recruited the prefrontal cortex during episodic memory retrieval in compensating their low cognitive control capacity [33]. Nevertheless, the underlying processes of episodic memory (especially the retrieval phase) affected by cognitive control training have not been reported yet.

Taken together, the present trial will examine the efficacy of cognitive training on episodic memory of aMCI patients. If cognitive training is effective in improving episodic memory function, then greater improvement should be observed in the training group than control group. Moreover, functional and structural data would provide further neural plasticity information about the training-related improvement.

## Methods/Design

### Study design

This is a single-center, randomized, double-blind, placebo-controlled trial registered at clinicaltrial.gov (NCT03133052). The study report will comply with the CONSORT statement and CONSORT-NPT (non-pharmacologic treatments) statement [34, 35]. The primary goal of this trial is to investigate whether cognitive control training can enhance episodic memory retrieval in aMCI patients. The secondary goal of this trial is to evaluate the efficacy of cognitive control training on neural plasticity in aMCI patients. The expected flow of patients through the trial can be seen in Fig. 1. The SPIRIT checklist with the recommended items to address in a clinical trial protocol is available (Additional file 1).

**Fig. 1 Fig1:**
[figure not shown]
*Flow chart* of the experimental design

### Participants

Seventy qualified individuals are currently being recruited from the memory clinic of the First Affiliated Hospital of Zhejiang University and randomly assigned to the cognitive training or control group.

### Inclusion criteria

Age > 55 years;Elementary school education or higher;Chief complaint of memory impairment confirmed by relatives;Ability to read a computer screen;Normal overall cognitive function as evidenced by Clinical Dementia Rating-global (CDR-global) = 0.5, Mini-mental State Examination (MMSE) score ≥ 22 with a concurrent Montreal Cognitive Assessment (MoCA) score ≤ 20 for those with elementary educational level and MMSE score ≥ 26 with a MoCA score ≤ 25 for those with junior educational level or above;Auditory Verbal Learning Test-Huashan version (AVLT-H) scores 1.5 standard deviations lower than age-matched controls;Activities of Daily Living assessment-20 (ADL-20) ≤ 23;Do not comply with AD diagnostic criteria proposed by the International Statistical Classification of Diseases and Related Health Problems, 10th Revision (ICD-10 for research use) and the National Institute of Neurological and Communicative Disorders and Stroke and Alzheimer’s Disease and Related Disorders Association (NINCDS-ADRDA).

### Exclusion criteria

Lack of a home computer or computer literacy;A medical history of stroke and nervous system lesions, cerebral infarction, encephalomalacia lesions, or other space occupying lesions detected by head MRI plain scan;Other nervous system diseases likely to cause brain dysfunction, such as schizophrenia, severe depression, frontotemporal lobe dementia, Huntington’s disease, brain tumors, Parkinson’s disease, metabolic encephalopathy, encephalitis, multiple sclerosis, epilepsy, brain trauma, or normal hydrocephalus;Other systematic diseases likely to impair cognition, such as hypothyroidism, deficiency of folic acid or vitamin B12, or viral infection (syphilis or HIV);Ethanol or drug misuse;Severe liver and renal insufficiency, pulmonary incompetence, anemia, malnutrition, gastrointestinal tract disease, arrhythmia, or heart infarction in the previous six months;Metal implantation or other MRI contraindications;Aphasia, consciousness disorder, or other diseases precluding cognitive examination;Use of drugs that affect cognitive function, such as sedatives, anti-anxiety drugs, nootropic drugs, sleeping pills, and cholinomimetic drugs.

### Randomization

All individuals are randomly and evenly assigned to the cognitive training or control group using the random number table method by an independent statistician using SAS software (SAS Institute, Inc., Cary, NC, USA). Written informed consent is obtained from all participants. After enrolment, the random and intervention number labels are sent to the memory clinic. If a participant needs emergency treatment, blinding will be broken, and the participant will then be managed as off-trial.

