### Sample size estimates

According to a previous study [41], in which computerized cognitive training was administered for six weeks, the mean difference in AVLT-H score between the cognitive training and control groups was 0.26 ± 0.3. Based upon this difference, 22 samples are required to yield a statistical power of 80% at a statistical significance level of 0.05. The sample size was estimated using the following equation:$$ n=\frac{\left({q_1}^{-1}+{q_2}^{-1}\right){\left({t}_{\alpha /2}+{t}_{\beta}\right)}^2{S}^2}{\delta^2} $$

where q_1_ and q_2_ are the sample size ratio of two groups (q_1_ = q_2_ = 0.5), α is the statistical significance level (α = 0.05), β is calculated from 1-β which stands for statistical power (1-β = 0.8), δ is the mean difference (δ = 0.26), and S is the standard deviation (S = 0.3) used in the analyses. Considering the instability of standard deviation and dropout rate, the sample size for each group is set as 35.

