### Statistical analysis

To make sure that baseline levels between groups (cognitive training, control) are comparable, questionnaire measures will be analyzed using independent sample t-tests. To determine the training efficacy from baseline to outcome, paired sample t-tests will be used in each group, respectively, for the changes in scores of trained tasks. The neuropsychological changes will be correlated with the score changes of the trained tasks to test the training effect on neuropsychological performance. To determine the training transfer effect, ANOVAs will then be performed on each dependent variable, with time (baseline, outcome) as the within-subjects factor and group (cognitive training, control) as the between-subjects factor.

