There are several limitations in this study. First, the test battery reported in this study is limited: in consideration of the individuals’ attention span and compliance, we do not include scales such as visual attention (e.g. Bells test, etc.), praxis (e.g. imitation of gestures, etc.), tests of reasoning (e.g. Raven matrices, etc.), verbal fluency (e.g. phonemic verbal fluency task, etc.), inhibition (e.g. Stroop test, etc.), and planning (e.g. Towers of London test, etc.). Second, the topic of this study is MCI due to AD. Theoretically, AD biomarkers should be performed (e.g. FDG-PET for mesial temporal glucose hypometabolism, PET-amyloid, etc.). However, it is inaccessible for every participant to perform AD biomarkers (e.g. low compliance and high expense). The diagnosis of MCI due to AD has to depend on clinical symptoms, neuropsychological tests, and MRI in this study.

One big challenge that we may meet for the study is the difficulty in maintaining participants. The aMCI patients who agree to participate in the study may decide to quit the program during the 12 consecutive weeks. Discontinuing from the intervention program may be attributed to personal issues (e.g. diseases, busyness, or low incentive) or family reasons (e.g. moving, need to care for their partner, or lack of caregiver’s supervision) that may impede them from completing the study. We calculated the dropout rate in the sample size estimation to make sure that we could reach adequate power for the study.

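### The off-trial rule and a power-only answer to dropout leave the week-12 AVLT-H comparison open to selective loss, of a size and direction the article does not fix

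*Protocol article*

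**What the plan says.** All places are in the protocol article.

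- **Randomization.** If a participant needs emergency treatment, "blinding will be broken, and the participant will then be managed as off-trial". The section does not say whether the week-12 assessment still takes place or whether the data are analysed.
- **Discussion (limitations).** Retention is named as a major challenge: "The aMCI patients who agree to participate in the study may decide to quit the program during the 12 consecutive weeks". Personal and family reasons for stopping are listed as possible obstacles to finishing the study. The stated response is that dropout was taken into account in the sample size so that power would be adequate.
- **Sample size estimates.** "22 samples are required to yield a statistical power of 80% at a statistical significance level of 0.05". Then: "Considering the instability of standard deviation and dropout rate, the sample size for each group is set as 35". No dropout rate is given.
- **Statistical analysis.** The between-group test is an ANOVA on each dependent variable, "with time (baseline, outcome) as the within-subjects factor" and group as the between-subjects factor.
- **Data collection.** There is one post-baseline assessment, after 12 weeks of training.

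**The concern.** With two time points, the group-by-time test in this ANOVA is the same as a two-sample comparison of change from baseline. A patient without a week-12 score has no change value and drops out of it, unless a missing-data method is added. The off-trial rule and the treatment of quitting both concern events after randomisation, and nothing stated keeps the outcome once they occur.

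The arms also differ in a way that could make loss selective. Training is adaptive and pushes each patient towards the limit of performance, whereas control stays at a fixed basic level on two tasks. If the patients who leave one arm differ from those who leave the other, the patients who remain are no longer comparable by randomisation. Raising 22 to 35 per group does nothing about that.

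**Working it through.** **1. The plan's own figure.** Inputs from Sample size estimates: δ = 0.26, S = 0.3, two-sided α = 0.05, power 80%, q1 = q2 = 0.5. The stated formula gives the total:

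N = (1/q1 + 1/q2)(t_α/2 + t_β)² S²/δ²

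- Normal quantiles: N = 41.8, or 21 per group.
- Iterated t quantiles: N = 43.8, or 22 per group.

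The stated 22 is reproduced as a per-group number (power 80.2%). Read as a total, 11 per group, it would give 49%.

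**2. What the rise to 35 buys.** If the whole margin were for dropout, it would allow a loss of 1 - 22/35 = 37.1%. This is an upper limit, because the article says the margin also covers uncertainty in the SD. With no dropout at all, 35 per group would tolerate an SD of about 0.388. At 20% loss (28 per group) power is still about 89%. Power is therefore well protected.

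**3. What it does not buy.** Let f be the loss in an arm and g the amount, in SDs, by which completers exceed leavers in that arm. With no true effect,

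bias = (f_T × g_T - f_C × g_C) × S

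If selection acts in the training arm only, with equal loss in both arms and S = 0.3 taken as the SD of the quantity compared:

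| Loss per arm | g | Bias | Share of 0.26 | Two-sided type I error |
|---|---|---|---|---|
| 20% | 0.25 | 0.015 | 6% | 5.4% |
| 20% | 1.0 | 0.060 | 23% | 11.6% |
| 37% | 0.25 | 0.028 | 11% | 6.1% |
| 37% | 1.0 | 0.111 | 43% | 23% |

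If f and g are the same in both arms, the bias is zero.

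**4. The planned change comparison.** I simulated 20,000 null trials per setting with 35 per arm. Training-arm loss was 36% (log-odds of leaving -0.6 per SD of the driving variable) and control loss was 20% at random. Baseline and week-12 scores had equal variance and a correlation of 0.5 to 0.7. None of these values is in the article. Bias is in SDs of the AVLT-H score, shown for correlation 0.5, then 0.7, and only completers are analysed.

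| Loss in training depends on | Bias, change comparison | Type I error | Bias, ANCOVA | Type I error |
|---|---|---|---|---|
| Week-12 score | +0.10, +0.06 | 6.4%, 5.9% | +0.15, +0.10 | 9.3%, 7.8% |
| Baseline score | -0.10, -0.06 | 6.3%, 6.1% | 0.00, 0.00 | 4.9%, 5.3% |
| Change itself | +0.20, +0.16 | 10.6%, 10.3% | +0.15, +0.13 | 9.4%, 9.6% |

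The sign depends on the mechanism. ANCOVA removes the bias when loss follows baseline. It does not remove it when loss follows the outcome or the change, and when loss follows the week-12 score it is more biased than the change comparison.

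**The case against.** Four objections carry weight.

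- **A reader might infer that the plan drops everyone who quits and analyses completers only.** The article does not say so. It names no analysis set, the week-12 visit is not made conditional on adherence, and an ANOVA can be run on imputed data. The full protocol or analysis plan may settle this, and silence in an article is not itself a fault. What stands is that the provisions actually stated point towards losing the outcome, and the one stated answer to dropout concerns power.
- **Off-trial may describe patient management only, and emergencies may be rare.** This is fair. The article knows of no adverse events from cognitive training, so emergency unblinding alone is unlikely to cause large loss. The wording is still open on whether assessment ends.
- **A reader might take 37% as the planned dropout, or conclude that the training arm will look better than it is with about 10% type I error.** Neither is supported. The 37% is a ceiling. An error near 10.6% needs loss that follows the change itself, or a comparison of week-12 scores alone with loss that follows those scores. For the planned comparison the bias can go against training.
- **Burden may not differ as feared.** Both arms have the same session length and frequency, difficulty rises only after good accuracy, and the Discussion expects adaptivity to help participation. Monotony could equally cause loss from control. This leaves the direction open but does not make loss equal.

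**Conclusion.** The point holds as a weakness in what is stated, not as a demonstrated bias. A post-randomisation off-trial rule with no provision for the week-12 outcome, dropout met only by sample size, and a test that needs both scores can together leave a comparison that is no longer the randomised one.

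Under the assumed 36% and 20% loss, the bias in the change comparison is about 0.06 to 0.10 SD in either direction, with type I error near 6%. It reaches about 0.20 SD and 10.6% if loss follows the change itself. With equal loss and selection in both arms there is none. The loss rates, the strength of selection and the baseline-outcome correlation are all assumptions. The change should be made because it is cheap and the retention problem is one the article itself expects.

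**What to change.** - **Randomization and Data collection:** state that stopping training or emergency unblinding does not by itself end the already scheduled week-12 AVLT-H assessment, unless consent is withdrawn. Emergency care is not affected. This matters most, because no analysis fully repairs loss that depends on the unseen outcome.
- **Statistical analysis:** compare all randomised patients by assigned arm on week-12 AVLT-H delayed recall, adjusted for baseline (ANCOVA). Impute missing scores from baseline variables already collected, such as AVLT-H, MMSE, MoCA, age and education.
- **Sensitivity analysis:** shift the imputed scores by a range of deltas, separately by arm, since ANCOVA and imputation from baseline do not cover loss driven by the outcome. Report loss and reasons by arm.

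The cost is a few sentences of protocol text, some effort to bring back patients who stopped training, and modest extra analysis. The sample size does not change.

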### Blinding

The participants, nurses, neuroimaging specialists, statisticians, and psychologists are all blind to group allocation. Data management, evaluation, and analysis will also be conducted blind to group membership.

### Intervention

Cognitive control training will be conducted using a computerized self-adaption training pattern (i.e. individually adjusted task difficulty to bring individuals to their performance maximum). Training tasks which were effectively used in previous studies will be adopted [36], including Flanker task [37], n-back working memory task [38], task switching [39], and Stroop task [40]. To guarantee adaptability to training difficulty, different levels of difficulty will be established as in previous studies with larger sample sizes. Briefly, at the beginning, each individual is assigned a task of similar difficulty. On each training day, the participants are required to complete five tasks three times, with 2 min for each training session (for a total daily test time of 30 min). For each task, the task difficulty will be advanced when the accuracy rate exceeds 80%. To adjust for individual variation in adaptability, the number of types of stimuli, the presentation probability of each type of stimuli, and the size and duration of a stimulus were systematically set. To keep a systematical setting, only one parameter will be adjusted; the remaining parameters will remain unchanged when the task difficulty is elevated. If the accuracy rate of a certain task exceeds 80% of normal counterparts, the task will be substituted for another of higher difficulty. The training program will be implemented five times weekly for 12 consecutive weeks.

In the control group, the training tasks include just the Flanker task and 1-back task. Importantly, a fixed, primary difficulty level will be set. The training tasks will be performed five times weekly, 30 min per session, for 12 consecutive weeks.

With the guidance of doctors, the initial training will be done in clinic and the rest of the training will be completed at home. The training will be supervised by an independent neurologist by telephone and the Internet.

